**Diagnosis and antibiotic combination***	
Difficulty swallowing liquids	Abnormal breathing
Difficulty swallowing solids	Airway obstruction
Dysphagia	Allergic cough
Dysphagia, oropharyngeal	Breathing difficulty
Dysphagia, unspecified	Breathing problem
Esophageal dysphagia	Chest congestion
Impaired swallowing	Chest heaviness
Intermittent dysphagia	Chronic cough
Laryngeal pain	Chronic coughing
Pain on swallowing	Congestion pulmonary
Pain or burning when swallowing	Cough
Pain with swallowing	Cough due to angiotensin-converting enzyme inhibitor
Painful swallowing	Cough secondary to angiotensin converting enzyme inhibitor (ACE-I)
Problems with swallowing	Coughing
Swallowing difficulty	Cryptogenic organizing pneumonia
Swallowing disorder	DOE (dyspnea on exertion)
Swallowing impairment	Dry cough
Swallowing pain	Dyspnea
Swallowing pain or burning	Dyspnea on exertion
Swallowing painful	Exertional dyspnea
Trouble swallowing	Hypercarbia
	Non-productive cough
	Nonproductive cough
	Other dyspnea and respiratory abnormality
	Productive cough
	Pulmonary edema
	Recurrent upper respiratory infection (URI)
	Respiratory tract infection
	Shortness of breath
	Shortness of breath dyspnea
	Shortness of breath on exertion
	SOB (shortness of breath)
	Trouble breathing
	URI (upper respiratory infection)
	Viral bronchitis
	DOE (dyspnea on exertion)

*Antibiotics: Oral penicillins, macrolides, cephalosporins, quinolones, tetracyclines

#### Risk calculator

The development team next looked at which patient-specific elements of the history and physical exam (auto-generated when possible) the tool could use to automatically calculate the risk probabilities and provide recommendations suggested by validated CPRs. While several alternatives including traditional CDS templates were considered, it soon became clear that dynamic flowsheets would be used because this functionality would enable the required calculations of CPRs while maintaining the hub-and-spoke linkages critical to successfully integrating CDS tools into workflow [15].

#### Bundled order sets, documentation, and patient instructions

The design specifications called for integrated bundled order sets, template documentation, and patient instructions that would be linked to each CPR in order to further enhance provider usability and buy-in. The team constructed bundled order sets tailored to each of the potential risk states calculated by the CPR tool. Three versions of the iCPR were created for strep throat--low-, intermediate-, and high-risk. Low risk led to a bundled order set without antibiotics, intermediate led to a workflow with rapid strep as the next step (with resulting low- or high-risk order sets), and high risk led to a bundled order set with pre-populated suggested antibiotic orders. The pneumonia iCPR had a similar format but with only low- and high-risk states. Clinical experts populated each bundled order set with the most common orders (antibiotics, symptom relief medications, *et al*.) used for strep throat and outpatient pneumonia treatment. They also guided the development of the clinical documentation that auto-populated the progress note of the visit, a key to enhancing the usability of the tool. Auto-generated patient instructions in English and Spanish were also developed for each risk state. The instructions outlined expected duration, etiology of the illness (viral or bacterial), triage steps for worsening symptoms, description of symptom relief medications, and contact information. Figure 2 represents a schematic flow of the iCPR tool. With the prototype iCPRs built, the team moved into the usability phase to evaluate the prototype's ability for workflow integration and for meeting the provider's preferences.

**Figure 2 F2:**
[figure not shown]
**Schematic flow of iCPR tool**.

#### Usability testing

We conducted usability testing to evaluate the main functionalities of the iCPR tool: alerting, risk calculator, bundled ordering, progress note, and patient instructions. Using 'think aloud' and thematic protocol analysis procedures, simulated encounters with eight providers using written clinical scenarios were observed and analyzed. Screencapture software and audiotaping were used to record all human-computer interactions. Themes were reviewed by the study team, and consensus was used to guide prototype refinements when technically and logistically feasible. A second round of usability testing with eight additional providers was conducted using trained actors to simulate 'live' clinical encounters. These additional data were coded using a time-series analytic procedure that focused on the workflow of encounters to help understand issues not generated in the scripted 'think aloud' scenarios. A full description of the usability testing design and findings is described separately (in preparation). These data were then reviewed, and additional modifications were incorporated into the prototype to achieve the final iCPR tools. Figures 3 and 4 depict the finalized components of the iCPR tool.

**Figure 3 F3:**
[figure not shown]
**Screenshots of finalized iCPR tool**.

**Figure 4 F4:**
[figure not shown]
**Magnified views of risk score calculator and bundled order set**.

### Trial design

#### Practice setting

The study was conducted at a large urban academic medical center. All of the providers were members of the academic primary care practice that is located on the main hospital campus. The outpatient clinic has over 55,000 visits annually and serves a diverse population that is approximately 56% Hispanic, 35% African-American, 7% white and 2% other.

#### Provider eligibility, consent, and randomization

All primary care providers within the medical practice were eligible for the study. The practice includes 149 primary care faculty, residents, and nurse practitioners divided into four units on the same floor. The study design was a randomized control trial in which the providers within the academic medical center outpatient practice were the unit of randomization. Faculty providers were randomized via random number generator to intervention or control in a 1:1 ratio. Medical residents were randomized within blocks according to their outpatient ambulatory care month (a period with substantially increased outpatient clinical activity) assignments to ensure even distribution throughout the academic calendar. However, due to changes in the resident calendar in year two of the study, any additional medical resident providers entering the system were added in a 1:1 fashion. Only providers randomized to the intervention are triggered by the EHR to use the iCPR tools. After randomization, all providers were invited to standardized educational forums for consent and training (if randomized to the intervention).

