**Methods:**

A multi-disciplinary design team was assembled to develop a prototype iCPR for validated streptococcal pharyngitis and bacterial pneumonia CPRs. The iCPR tool was built as an active Clinical Decision Support (CDS) tool that can be triggered by user action during typical workflow. Using the EHR CDS toolkit, the iCPR risk score calculator was linked to tailored ordered sets, documentation, and patient instructions. The team subsequently conducted two levels of 'real world' usability testing with eight providers per group. Usability data were used to refine and create a production tool. Participating primary care providers (n = 149) were randomized and intervention providers were trained in the use of the new iCPR tool. Rates of iCPR tool triggering in the intervention and control (simulated) groups are monitored and subsequent use of the various components of the iCPR tool among intervention encounters is also tracked. The primary outcome is the difference in antibiotic prescribing rates (strep and pneumonia iCPR's encounters) and chest x-rays (pneumonia iCPR only) between intervention and control providers.

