#### Patient inclusion and exclusion criteria

There was no specific patient inclusion/exclusion criteria used in iCPR. The initial plan had been to use age, prior hospitalization history, and current/recent antibiotic use as criteria, but these were eliminated due to a variety of reasons, including inadequate/inaccurate documentation of prior medical history and current medication prescription. Thus, other than being an enrolled intervention provider, the only criteria for inclusion were the appropriate triggering diagnoses, chief complaint, or a diagnosis/order combination. The list of chief complaints and related diagnoses and orders that trigger each iCPR is listed in Table 1. Common triggers include a chief complaint or diagnosis of 'sore throat' for the strep throat iCPR and a diagnosis of 'bronchitis' for the pneumonia iCPR.

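### Providers are asked for consent after allocation, at a forum that trains only one arm, so refusal can depend on arm; the analysis should be fixed on all randomised providers.

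*Protocol article*

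**What the plan says.** All references are to the protocol article.

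- **Unit and allocation** (Provider eligibility, consent, and randomization): "the providers within the academic medical center outpatient practice were the unit of randomization". For faculty, "Faculty providers were randomized via random number generator to intervention or control in a 1:1 ratio". For residents arriving after the calendar changed in year two, "any additional medical resident providers entering the system were added in a 1:1 fashion".
- **Consent** (same section): "After randomization, all providers were invited to standardized educational forums for consent and training (if randomized to the intervention". No step is described that hides the arm until consent has been given.
- **Training** (Provider Training): everyone assigned to the tool had a session of about 45 minutes, individually if they missed the group session.
- **Alerts** (Restriction of alerts): the tool is switched on by randomised assignment. Consent is not mentioned as a condition.
- **Which encounters qualify** (Patient inclusion and exclusion criteria): "other than being an enrolled intervention provider, the only criteria for inclusion were the appropriate triggering diagnoses, chief complaint, or a diagnosis/order combination".
- **Comparison** (Outcome): antibiotic prescriptions are compared between providers according to the arm they were randomised to.
- **Model** (Statistical Analysis): a GEE clustered on clinician, with treatment arm as the sole covariate.
- **Status** (Implementation): the trial is described as ongoing.

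**The concern.** Randomisation makes the two groups of providers comparable at the moment of allocation. If a provider can then withdraw knowing the arm, and withdrawal also removes that provider's encounters, the groups compared are no longer the groups randomised.

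The two arms are not asked for the same thing. An intervention provider is asked to attend training and to work with a new tool. A control provider is only observed, through the simulated triggering described under Process. Reasons to decline can therefore differ by arm. Willingness to take on a tool that questions antibiotic use is plausibly related to how much the provider prescribes, which is the outcome.

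A model with arm as its only covariate has no means of correcting for selective loss of clusters. At stake is part of the estimated effect: a spurious reduction if heavy prescribers decline the tool, or a masked effect if light prescribers decline it.

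**Working it through.** **1. What the planned effect of 12 means.** The bias needs a yardstick, so the reading of 12% in Power Calculation was checked first.

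- Inputs: 30% baseline, alpha 0.05 (taken as two-sided), 80% power, ICC below 0.15, 535 subjects per condition, 149 providers.
- Absolute reading, 30% against 18%: n per arm = [1.96 × √(2 × 0.24 × 0.76) + 0.8416 × √(0.30 × 0.70 + 0.18 × 0.82)]² / 0.12² = 198 rounded up, or 396 per condition.
- Clustering: m = 535/149 = 3.59. At the ICC bound of 0.15 the inflation is 1 + 2.59 × 0.15 = 1.389, and 396 × 1.389 = 550, within 3% of 535.
- Relative reading, 30% against 26.4%: 4,904 per condition before clustering, far from 535.

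The planned effect is therefore 12 percentage points. The match is conditional, because the ICC is given only as a bound.

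**2. Shift caused by dropping decliners.** Suppose the tool has no effect, refusal occurs in the intervention arm only, a share r of that arm's encounters is dropped, and decliners prescribe d above the arm's mean. Then:

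shift = −r × d / (1 − r)

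Neither r nor d is in the article. For illustration, decliners are taken to prescribe at 45% against a mean of 30% (d = 0.15). Half of 149 is about 75 providers, so 10% is about 7 and 20% about 15.

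| r | Rate left in arm | Shift | Share of 12 points |
|---|---|---|---|
| 0 | 30.0% | 0 | 0 |
| 10% | (0.30 − 0.10 × 0.45)/0.90 = 28.3% | −1.7 points | 14% |
| 20% | (0.30 − 0.20 × 0.45)/0.80 = 26.25% | −3.75 points | 31% |

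If decliners instead prescribe at 15% (d = −0.15), the signs reverse: (0.30 − 0.10 × 0.15)/0.90 = 31.7% and (0.30 − 0.20 × 0.15)/0.80 = 33.75%, shifts of +1.7 and +3.75 points.

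**3. Shift when decliners differ less sharply.** Provider rates were drawn from a beta distribution with mean 30%. The odds of refusing doubled per standard deviation of prescribing, and no control provider refused. The between-provider SD is √(ICC × 0.30 × 0.70), that is 0.177 at ICC 0.15 and 0.102 at ICC 0.05.

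| Refusal | ICC 0.15 | ICC 0.05 |
|---|---|---|
| 10% | −1.3 points | −0.7 points |
| 20% | −2.5 points | −1.4 points |
| 30% | −3.6 points | −2.0 points |

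At 10% refusal these correspond to decliners prescribing at about 42% (d = 0.0133 × 0.90/0.10 = 0.12) and 37% (d = 0.0074 × 0.90/0.10 = 0.07), so the 45% used in step 2 is towards the high side.

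**4. The passages on who is analysed.** The Outcome section speaks of randomised providers. The patient criteria section speaks of enrolled intervention providers. With consent before randomisation these would be the same people. With consent afterwards they can differ, and the article does not say which group supplies the encounters when they do.

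**The case against.** The strongest reply is that the article gives no sign of loss and points towards an analysis as randomised.

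- **Training was complete in the intervention arm** according to Provider Training, and that is the arm where refusal would be expected. This stands as evidence of little loss there. It reports training and not consent, says nothing about controls, and cannot cover residents yet to arrive.
- **The count did not fall.** The practice section states "The practice includes 149 primary care faculty, residents, and nurse practitioners divided into four units on the same floor", and the abstract states "Participating primary care providers (n = 149) were randomized and intervention providers were trained in the use of the new iCPR tool". The two numbers agree, but the abstract's is a count at randomisation and does not show how many consented in each arm.
- **The comparison is by randomised arm** in the Outcome section. This stands, and it is close to the remedy proposed here. The detailed definition of the analysis set is also commonly left to an analysis plan, which is not shown. So the point is the stated order of consent and the two unreconciled terms, and not a missing definition.

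A reader might infer more than the article supports, in four ways:

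- **That decliners are dropped, because inclusion requires "other than being an enrolled intervention provider".** That phrase concerns which encounters trigger the tool. Taken as the analysis set it would exclude every control encounter, so it cannot settle how decliners are treated.
- **That consenting is what brings the alerts.** The article ties them to randomised assignment.
- **That year-two residents were allocated without a random procedure.** The wording gives no evidence of this, and it is a separate matter from consent.
- **That the tool would necessarily look better than it is.** The direction depends on who declines.

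**Conclusion.** The point holds as a design weakness with a conditional consequence. It is stated plainly that consent follows allocation, at a forum whose content differs by arm, so arm-dependent refusal of whole clusters is possible. It is not shown that refusals occurred, or that a decliner's encounters would be left out.

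The selection bias is exactly zero if nobody refuses or if every randomised provider is analysed. If 10% to 20% of the intervention arm refused, no control did, and decliners were excluded, the shift would be about 0.7 to 3.75 points (roughly 1 to 4), or 6% to 31% of the planned 12. Those figures rest on assumed refusal rates, assumed prescribing by decliners and, in the simulation, an ICC of 0.05 to 0.15. They show scale and are not an estimate for this trial.

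**What to change.** 1. **Providers still to enter:** obtain consent before the allocation is disclosed, and hold the training session afterwards for those assigned to the tool.
2. **All providers, including those already randomised:** reconcile the patient criteria section with the Outcome section. State that the primary set is the eligible encounters of every randomised provider, analysed in the allocated arm regardless of training attendance or tool use, and regardless of consent where the ethics board permits use of routine record data.
3. **If that permission is refused:** report refusals by arm and add a sensitivity bound. With refusal shares r_I and r_C and decliner excesses d_I and d_C, excluding decliners shifts the difference (intervention minus control) by −r_I × d_I/(1 − r_I) + r_C × d_C/(1 − r_C). Put in the observed refusal shares (as shares of encounters, or of providers as an approximation) and a stated range for the excesses, with both signs.

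The cost is a small change in the enrolment sequence and possibly a waiver request. Reordering consent cannot help providers already randomised; for them the second step does the work. Outcome data come from the electronic record and control encounters are already captured by simulation, so the main obstacle is permission to use the data.

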#### Provider Training

All providers allocated to the intervention received approximately 45 minutes of training on how the iCPRs are integrated into the EHR and how to interpret the output of each iCPR. Each training session was led by at least one study investigator and one study staff member. The training consisted of a background on the strep throat and pneumonia CPR evidence, several walkthroughs of iCPR tools using the EHR training version, and a demonstration video simulating the tool in a live clinical encounter. Providers who were unable to attend group training sessions were trained individually.

#### Patient inclusion and exclusion criteria

There was no specific patient inclusion/exclusion criteria used in iCPR. The initial plan had been to use age, prior hospitalization history, and current/recent antibiotic use as criteria, but these were eliminated due to a variety of reasons, including inadequate/inaccurate documentation of prior medical history and current medication prescription. Thus, other than being an enrolled intervention provider, the only criteria for inclusion were the appropriate triggering diagnoses, chief complaint, or a diagnosis/order combination. The list of chief complaints and related diagnoses and orders that trigger each iCPR is listed in Table 1. Common triggers include a chief complaint or diagnosis of 'sore throat' for the strep throat iCPR and a diagnosis of 'bronchitis' for the pneumonia iCPR.

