#### Alerts, overrides and triggers

Alerts are an active research area in the CDS literature. They can be categorized on two spectrums of activity: active versus passive and mandatory versus optional. A major early design consideration was the whether to use active (interrupting) or passive (non-interrupting) alerts [15,16]. In the context of our commercial EHR, active alerts 'pop-up' at the user, directly interrupting their workflow in order to draw their attention. Passive alerts are non-interrupting, minimally intrusive alerts, and would use non-interrupting flags or highlights to draw the CDS alert. Mandatory alerts require the user to take the designated action or explain the reason for overriding the CDS, while optional alerts allow the user to ignore the CDS alert without an explanation. Prior literature has demonstrated the superior efficacy of active mandatory alerts; however they are more disruptive to workflow, which contributes to the low uptake of CDS tools [10]. Their use is also problematic in the increasingly crowded CDS dashboards populating the primary care EHR. Balancing these factors, the development team selected a two-step system in which an early-in-workflow passive mandatory alert and a later-in-workflow active mandatory alert were combined. Mandatory alerts were chosen for both because data on reasons for declining the CDS tool were critical to iterative improvements.

Another major design issue was the choice of where in the primary care workflow the alert should launch and what the specific trigger diagnoses or orders should be. The pros and cons of various workflow triggers options were discussed and consensus was achieved for the initial prototype. The agreed trigger points for the tool were one of three workflow locations: chief complaint, relevant and specific encounter diagnoses, or a less specific encounter diagnosis in combination with a relevant antibiotic order (Table 1 lists the relevant trigger diagnoses and orders). The early-in-workflow passive mandatory alert triggered from the chief complaint, while the later-in-workflow active mandatory alert triggered from diagnosis and/or orders to ensure users did not simply forget to use the CDS tool.

**Table 1 T1:** Chief complaint, diagnosis, and diagnosis/antibiotic combination triggers of iCPR tools

Strep	Pneumonia

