### Follow-up

#### Process

The process measurement battery is designed to assess the uptake of the iCPR tool by providers and to document the utilization of each part of the tool. This is a critical outcome because poor provider utilization of CDS and other EBM and quality improvement tools has been a frequent barrier to their success [9]. Measured markers of utilization (see Table 2) include rate of accepting the iCPR tool when triggered in an encounter, using the relevant iCPR risk calculator, use of the bundled order set linked to each risk calculator score, and use of each section of the bundled order set (orders, documentation, patient instructions, *et al*.). The rate of triggering of the iCPR tool from the various sections of the EHR will be measured in the intervention and control arm. The control arm is measured through 'shadow' simulation of the iCPR tool in the control patients, which allows comparison of triggering rates in the control and intervention.

**Table 2 T2:** Outcome measures

CPR	Process Outcomes	Primary Outcome	Secondary Outcomes
Pneumonia	% of eligible encounters accepting iCPR and using bundled order set	Number of antibiotics prescribed	Number of chest x-ray ordered
Strep throat	% of eligible encounters accepting iCPR and using bundled order set	Number of antibiotics prescribed	Number of rapid strep tests and throat cultures ordered

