#### Outcome

The outcome measurement battery is designed to detect changes in clinical practice that are most likely to result from use of the iCPRs. The primary outcome is the difference in antibiotic prescribing frequency among patient encounters eligible for the iCPR tool among intervention compared to control providers. For example, for all patients presenting with symptoms that launch the pneumonia or strep throat tools, data will be collected from the EHR on the number of prescriptions for antibiotics written by providers randomized to the iCPR compared to usual-care arms, respectively. We will also examine the rate of chest x-ray orders and rapid strep throat test orders between intervention and control providers as a secondary outcome (see Table 2).

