### Statistical Analysis

The planned statistical analyses include comparing socio-demographic and other baseline characteristics. Patient comparisons will be conducted by stratifying the sample by randomization status and by condition (*i.e.*, pharyngitis and pneumonia). We will use the t-test, Wilcoxon test, or the chi-square test, as appropriate, to evaluate the balance between groups. The relative frequency of triggering of each iCPR in intervention and control patients, overall, and by where the triggering occurs (chief complaint, ordering, or diagnosis) will then be compared. We will calculate the proportion of intervention encounters in which each component of the iCPR tool, including the overall tool, the risk calculator, and the bundled order set, are used. This calculation will be repeated stratifying by test condition and by provider characteristics (training level, *et al*.). To test the effect of iCPR, we will use a generalized estimating equation model with clinician as the cluster variable, antibiotic prescribing as the outcome variable, and intervention group as the only explanatory variable. Given the nature of the possible relationship between patients in a cluster, we will use an exchangeable correlation structure for parameter estimation.

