### Power Calculation

Sample size was calculated as if individuals were independent, and then adjusted to account for the clustering of patients within physicians. Although patient outcomes are assumed to correlate somewhat within provider, the multicausal nature of clinical outcomes and the likely random nature of patient assignment to providers led us to estimate a small interclass correlation (intraclasss correlation coefficient for binomial response < 0.15). The calculation of sample size was performed with a significance level of 0.05 and 80% power. The adjusted sample size was calculated by multiplying the initial estimate of the number of patients by an inflation factor, which is a function of the interclass correlation and the number of the clusters. Final calculations estimated a need of 1,070 study subjects (535 in each disease condition) in total assuming a baseline rate of 30% antibiotic ordering in each condition and an estimated effect size of a 12% reduction in ordering in the intervention arm.

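### Some encounters enter the denominator of the antibiotic-prescribing outcome only because an antibiotic was ordered, so the primary comparison is partly conditioned on its own outcome

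*Protocol article*

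**What the plan says.** The section on alerts, overrides and triggers gives three routes to a trigger: a chief complaint, a specific diagnosis, or "a less specific encounter diagnosis in combination with a relevant antibiotic order". Table 1 lists the diagnoses for the third route (cough, URI, dyspnea and swallowing terms among them), and its footnote defines the order: "Antibiotics: Oral penicillins, macrolides, cephalosporins, quinolones, tetracyclines".

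The patient criteria section makes all three routes inclusion criteria: "the only criteria for inclusion were the appropriate triggering diagnoses, chief complaint, or a diagnosis/order combination". The Outcome section then states: "The primary outcome is the difference in antibiotic prescribing frequency among patient encounters eligible for the iCPR tool among intervention compared to control providers". Under Process, "The control arm is measured through 'shadow' simulation of the iCPR tool in the control patients", so the same triggers are evaluated in both arms.

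The Statistical Analysis section plans to compare triggering overall and "by where the triggering occurs (chief complaint, ordering, or diagnosis) will then be compared". The effect of the tool is tested by a GEE model clustered on clinician, with study group as its only covariate. Nothing in that section removes or separates order-triggered encounters. The Power Calculation section plans 535 subjects per condition, "assuming a baseline rate of 30% antibiotic ordering in each condition".

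**The concern.** Take an encounter with a less specific Table 1 diagnosis and no other trigger. It is counted only if the outcome event, an antibiotic order, has occurred. In usual care such encounters show a prescribing rate of about 100% by construction, apart from cancelled orders. The same visit without an order is counted in neither arm.

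The intervention is meant to change that event, and it can act in two ways:

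- **Order never started.** Training, or carry-over from earlier use of the tool, may lead a provider not to order. The visit then leaves the denominator instead of counting as a non-prescription.
- **Order cancelled after the alert.** The article does not say whether such a visit stays eligible, or whether the shadow simulation treats a cancelled control order the same way.

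In both cases the analysed rate is not a prescribing rate for a defined population, and the between-arm difference may not be the effect that the trial means to estimate.

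**Working it through.** **The plan's own figure.** Read 30% versus 18% as a 12-point absolute reduction, with two-sided alpha 0.05 (sidedness is not stated) and 80% power. With p̄ = 0.24:

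n per arm = [1.96·√(2·0.24·0.76) + 0.842·√(0.30·0.70 + 0.18·0.82)]² / 0.12² ≈ 198, or 396 per condition.

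With 149 providers, m = 535/149 = 3.59. The design effect 1 + (m − 1)·ICC is 1.363 at ICC 0.14 and 1.389 at 0.15, giving 396 × 1.363 = 540 and 396 × 1.389 = 550. The stated 535 is reproduced within 3%. It rests on 30% and 18% being true prescribing rates in the analysed set.

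**Illustration.** The article gives no trigger mix, so these inputs are assumptions. Per arm there are 600 visits eligible without an order and 400 with only a less specific diagnosis. True control prescribing is 30% in both groups.

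- Prescriptions: 0.30 × 600 = 180 and 0.30 × 400 = 120.
- Control denominator: 600 + 120 = 720, since the other 280 non-specific visits are never counted.
- Control rate: (180 + 120)/720 = 41.7%.

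Where prescribing falls from 30% to 18%, the intervention counts become 108 of 600, 72 of 400, or both. Two readings of eligibility are possible. On *final orders*, only the 72 remaining non-specific prescriptions are counted. With *cancelled orders retained*, the whole fall is taken to come from cancellations after the alert, so all 120 stay in the denominator.

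| Where prescribing falls | True difference over all 1,000 visits | Final orders | Cancelled orders retained |
|---|---|---|---|
| Everywhere | 12.0 | 41.7 − 180/672 (26.8) = 14.9 | 41.7 − 180/720 (25.0) = 16.7 |
| Order-independent visits only | 0.6 × 12 = 7.2 | 41.7 − 228/720 (31.7) = 10.0 | 10.0 |
| Non-specific visits only | 0.4 × 12 = 4.8 | 41.7 − 252/672 (37.5) = 4.2 | 41.7 − 252/720 (35.0) = 6.7 |

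Within the order-only stratum, final orders give 100% versus 100%, and retention gives 100% versus 72/120 = 60%.

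**Range.** Let u be the number of non-specific visits per order-independent visit. With the same prescribing rate p in both groups, the counted rate is (p + u·p)/(1 + u·p). For u from 0.25 to 3 with a uniform fall from 30% to 18%, the control rate runs from 34.9% to 63.2%. The apparent difference is 13.4 to 16.5 points on final orders and 14.0 to 25.3 with cancelled orders retained, against a true 12.

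**No effect.** If neither prescribing nor coding changes, both arms give 300/720.

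**The case against.** Five points can be made for the plan.

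- **The affected share may be small.** The patient criteria section names sore throat and bronchitis as common triggers, and neither needs an order. Table 1 also overlaps: dysphagia is a stand-alone chief complaint, and productive cough and pain on swallowing are stand-alone diagnoses. This stands; the size is unknown.
- **The rule is the same in both arms.** A reader might infer that the randomised comparison is invalid or that false positives are inflated. The documents do not support that. With no change in prescribing or coding and like handling of orders, both arms are selected alike.
- **The alert fires after the order.** A reader might infer that success in the third route can never be seen. That holds on final orders but not if visits with cancelled orders stay eligible, and the article is silent on which applies.
- **The 30% baseline.** A reader might infer that it is impossible for the mixed set. It is not: with a 5% order-only share the remaining visits need (0.30 − 0.05)/0.95 = 26.3%, and with 10% they need 0.20/0.90 = 22.2%. Only a large share strains it (at 29%, 0.01/0.71 = 1.4%).
- **Alert logic and analysis set may be separate.** The patient criteria are worded around intervention providers, and the Outcome section's example speaks of presenting symptoms. But that is only an example, and the stated outcome uses eligibility for the tool. The planned comparison of triggering by location could reveal differential entry, but it does not correct the primary estimate.

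**Conclusion.** The defect stands as a matter of definition: an antibiotic order admits some encounters to the denominator of an antibiotic-prescribing rate, and the primary model does nothing about it. What is harmed is the size and meaning of the estimated effect.

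Its magnitude cannot be fixed from the article. Under the assumed 600/400 mix, a uniform 12.0-point fall reads as 14.9 or 16.7 points. A fall confined to order-independent visits, worth 7.2 points overall, reads as 10.0. A fall confined to non-specific visits, worth 4.8 overall, reads as 4.2 or 6.7.

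The direction is therefore not fixed. Most of these cases overstate the difference, and the one understatement is 0.6 points. A reader might set the 10.0 against 12.0 and infer a material understatement, but 12.0 is the effect in only 600 of the 1,000 visits, so 7.2 is the like-for-like comparator. All these figures rest on the assumed mix and on equal control prescribing in the two groups.

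**What to change.** Leave the alert rules unchanged, and separate the firing of an alert from membership of the analysis set.

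1. Define the primary analysis set as encounters with a chief-complaint or stand-alone-diagnosis trigger, found by the same EHR query in both arms.
2. Report encounters that qualify only through the diagnosis/order combination separately. State whether a cancelled order keeps the encounter eligible, and apply the same rule in the shadow simulation.
3. Add a sensitivity analysis of all encounters carrying any Table 1 complaint or diagnosis, whether or not an antibiotic was ordered.
4. Add a second one limited to chief-complaint triggers. Stand-alone diagnoses are also entered after randomisation and may respond to the tool, so step 1 alone does not remove all dependence on the intervention.
5. State the planning baseline for the set actually analysed. If 30% and 18% hold there, 535 per condition needs no change on this account.

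The cost is one change to the denominator definition and its query; trigger location and shadow triggering are already captured. The primary set is somewhat smaller and accrual to 535 per condition slower. Under the assumed mix, the present rule counts 672/600 = 1.12 to 720/600 = 1.20 encounters for each one in the new set.
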